## Methods/Design

### Objectives

To determine whether a more gradual dose prescription with de-escalation of the elective radiation dose and the introduction of an intermediate dose-level in the treatment of head and neck cancer will result in less radiation sequelae and improved quality of life after treatment (toxicity) without compromising the recurrence rate in electively irradiated lymph nodes (safety).

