### Study design

This is a multicenter, phase III, single-blinded, randomized controlled trial.

Treatment allocation at randomization will be at a ratio of 2:1 in favor of the intervention arm. Randomization will be balanced for institution, tumor-site, T- and N-stage, and human papillomavirus status using minimization with a random element. Randomization and clinical trial data management is provided by the IKNL clinical research department.

A flow chart giving an overview of the study design is shown in Fig. 1.

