### Sample size calculation

This study was designed to detect a 10-point difference on the PSS-HN ‘normalcy of diet’ score at 12 months after radiation therapy with a power of 90% at a two-sided significance level of 0.05. An average ‘normalcy of diet’ score of 70 is expected after standard treatment. To achieve this significance level with an unequal randomization ratio (2:1), a total of 300 patients needs to be included.

The current rate of recurrence in electively irradiated lymph nodes was estimated to be 5% at 2 years after treatment [17]. An equal rate of recurrence is expected in the intervention arm, despite elective dose de-escalation. A recurrence rate of ≥10% will be considered clinically relevant and unacceptable. This difference can be detected with the number of patients planned for the primary outcome of the study and a one-sided α = 0.10.

The total duration of this trial is estimated to be 6 years (4 years accrual, 2 years follow-up).

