### Statistical analysis

All analyses concerning treatment effects will be done according to the intention to treat principle. The student’s t-test will be used to compare ‘normalcy of diet’ scores at 1 year after treatment, the primary endpoint of this trial. A Kaplan-Meier estimate will be calculated for the actuarial rate of recurrence in electively irradiated lymph nodes at 2 years after treatment. Actuarial rates on recurrence and survival will be determined by the date of histopathological diagnosis. Differences between the treatment arms will be assessed using the log-rank test.

For each quality of life questionnaire, data will be included in the analysis if a patient filled in the questionnaire at least at start and at one time-point during the study. Differences in quality of life over time between the intervention- and control arm will be analyzed by using a linear mixed model for repeated measurements. Difference in quality of life scores ≥10 points will be considered clinically relevant [32].

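### The 300 patients give only about 60% power to detect 10% versus 5% elective-node recurrence, and the planned log-rank test does not control the error of concluding that control is uncompromised

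*Protocol article*

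**What the plan says.** The Objectives section wants less toxicity "without compromising the recurrence rate in electively irradiated lymph nodes (safety"). Study design fixes the allocation: "Treatment allocation at randomization will be at a ratio of 2:1 in favor of the intervention arm".

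The Sample size calculation first sizes the trial on normalcy of diet and concludes that "a total of 300 patients needs to be included". It then turns to safety:

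- The benchmark is 5% at 2 years under current treatment, and the same figure is anticipated after de-escalation.
- The limit of acceptability is set next: "A recurrence rate of ≥10% will be considered clinically relevant and unacceptable".
- Adequacy of the sample for safety is then asserted in these words: "This difference can be detected with the number of patients planned for the primary outcome of the study". The alpha attached to this is 0.10, one-sided.

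No power is given for this comparison.

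Statistical analysis plans a Kaplan-Meier estimate of the 2-year recurrence rate, then adds: "Differences between the treatment arms will be assessed using the log-rank test". Safety assurance applies a one-sided log-rank boundary (critical value 1.728, nominal alpha 0.042) after every five recurrences, for an overall one-sided alpha of 0.10.

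**The concern.** There are two linked problems. First, the article asserts that a doubling from 5% to 10% is within the trial's reach, and its own figures do not bear this out. Second, the safety aim is to show that recurrence has not been made worse, while the only between-arm test described looks for a difference. In such a test alpha limits false alarms when the arms are equal. Missing a true 10% rate is the type II error, which is limited only by power, and here the power is low.

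The intervention lowers the elective dose, so the safety result carries half of the trial's stated objective. If the safety claim has no controlled error rate at the level the protocol calls unacceptable, a favourable toxicity result cannot be weighed properly against it.

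**Working it through.** **Inputs from the article.** N = 300 at 2:1, so 200 intervention and 100 control. Two-year recurrence is 5% in control, with 10% as the unacceptable rate. One-sided alpha is 0.10, so z = 1.2816. No losses are assumed at first.

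**The plan's own figures.** There is no stated safety power to reproduce. The monitoring figures do reproduce: 1.728 corresponds to a one-sided 0.0420, and four equally spaced looks at 1.728 give an overall 0.1004. Four looks of five events is 20 events. A fifth look would bring the overall alpha to 0.112.

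**Power of one final test, 10% versus 5%.**

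1. Two proportions, unpooled. SE = sqrt(0.05×0.95/100 + 0.10×0.90/200) = sqrt(0.000925) = 0.0304. Then 0.05/0.0304 = 1.644, and 1.644 − 1.282 = 0.362. Power is 64%.
2. Two proportions, pooled null variance. The pooled rate is 25/300 = 0.0833. Null SE = sqrt(0.0833×0.9167×(1/100 + 1/200)) = 0.0339. Then (0.05 − 1.2816×0.0339)/0.0304 = 0.218. Power is 59%.
3. Schoenfeld. HR = ln(0.90)/ln(0.95) = 2.054, so ln HR = 0.720. Expected events are 200×0.10 + 100×0.05 = 25. Then sqrt(25×2/9)×0.720 − 1.282 = 0.415. Power is 66%.
4. Freedman's formula at 2:1 gives 57%.
5. Simulated log-rank (20,000 trials, uniform 4-year accrual, 2 years of follow-up per patient): 60%. With an assumed 20% to 30% lost to death or censoring by 2 years, 55% to 56%.

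**Events and patients needed.** By Schoenfeld, 80% power needs (1.2816 + 0.8416)²/(2/9 × 0.720²) = 39.2 events, and 90% needs (1.2816 + 1.2816)²/(2/9 × 0.720²) = 57.1. By two proportions, 80% needs about 573 patients and 90% about 816.

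**Power under the 1.728 boundary.** By normal approximation, crossing at any look has 52% power with four looks and 60% with five. In simulation it is 47% at the five-event looks, or 50% if a final look at 1.728 is added.

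**The same inputs read as non-inferiority.** Take both rates as 5%, a margin of 10 − 5 = 5 points and one-sided 0.10. SE = sqrt(0.05×0.95×(1/100 + 1/200)) = 0.0267. Then 0.05/0.0267 − 1.282 = 0.592, and power is 72%. Simulating the Kaplan-Meier difference with a one-sided 90% upper bound gives about 75% at equal 5% rates, or 70% with an assumed 25% loss. At 10% versus 5% the rule wrongly declares safety in about 8% to 9% of trials. By formula, 80% power would need about 387 patients.

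**The case against.** **The article may intend non-inferiority.** Equal expected rates, an unacceptable limit and a one-sided alpha are the language of non-inferiority. On that reading alpha 0.10 would control the error that matters. This has force as a statement of intent. But the test described under Statistical analysis and Safety assurance is a log-rank comparison for a difference, no bound on the excess is tested, and power on this reading is still only about 72%.

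**The limit is an absolute rate.** Testing the 200 intervention patients against a fixed 5% has about 91% power at 10% (15 or more events, exact alpha 0.078). The arithmetic is right, but Safety assurance explicitly compares the two arms, so this is not the planned test.

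**Non-significance is nowhere equated with safety.** A reader might infer that a non-significant log-rank result will be reported as safe, and hence that the plan wrongly declares safety in 4 of 10 trials. The article states no such rule. The supportable claim is narrower: the decision rule is missing, and the one comparative test supplied does not control that error.

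**The boundary figures can be made to look worse than they are.** Applying 1.728 once to the final data gives 39%, but this ignores the earlier looks and is not the plan's power. Likewise, an observed 20/200 versus 5/100 has z = 1.48. That falls short of 1.728 but is significant at the 1.282 on which the 60% rests. Combining the interim boundary with a final test at 1.282 raises detection only to about 64%.

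**Other safeguards exist.** This is a secondary endpoint. The article provides central review of regional recurrences, serious-adverse-event reporting of elective-node recurrences, repeated looks and an independent committee. It also plans to estimate the 2-year rate itself, so a reader should not infer that the absolute rate is ignored. These measures help patients during the trial but do not supply a final inference.

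**Conclusion.** The point stands in this limited form. The adequacy statement in the Sample size calculation is not supported by the article's own inputs: a single between-arm test would miss a true 10% versus 5% in about 4 of 10 trials. It contradicts no stated power, because none is given. For a safety aim of no compromise, the article offers a difference test and no final decision rule.

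The figures rest on complete 2-year follow-up, constant hazards and the stated 5% control rate; losses lower them. The 5-point margin follows from the article's 5% and 10% but is not stated there.

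**What to change.** 1. In the Sample size calculation, replace the adequacy statement by the actual figures: about 60% power for a one-sided 0.10 test of harm at 10% versus 5%, and about 72% to 75% for non-inferiority if both rates are 5%.
2. In Statistical analysis, base the final safety conclusion on the Kaplan-Meier estimates already planned. Report the 2-year difference, intervention minus control, with a one-sided 90% upper bound. Conclude that control is not compromised only if the bound is below 5 percentage points, with the sponsor to confirm that margin.
3. Keep the log-rank boundary for interim monitoring, and state that a non-significant log-rank test is not evidence of safety.

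The cost is wording only, with no added patients or data. The stated safety power becomes less favourable, and about a quarter of trials would be inconclusive on safety even if the arms were truly equal. The fix does not raise the number of events; it makes the remaining uncertainty visible and controls the wrong-conclusion error.

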### Pre-treatment evaluation

Pre-treatment evaluation will include physical examination and flexible endoscopy of the upper aerodigestive tract, biopsy of the tumor, MRI and/or CT-scan of the head and neck area, and US of the neck including FNAC of cervical lymph nodes. All patients are evaluated by a multidisciplinary head-and-neck oncology team.

### Radiation therapy planning FDG-PET/CT-scan

In order to ensure that in the multicenter setting of this trial, the acquired quantitative data and standardized uptake value (SUV) recoveries are interchangeable between study sites, all FDG-PET/CT-scans will be acquired on EARL accredited scanners (http://earl.eanm.org) following the European Association of Nuclear Medicine (EANM) procedure guidelines for tumor PET imaging v2.0 [18].

FDG-PET/CT-scans of the head and neck area will be acquired in radiation therapy treatment position using a custom-made thermoplastic head, neck and shoulders mask to immobilize the patient during radiation therapy and the scanning procedures. A diagnostic CT-scan using an intravenous contrast agent will be acquired in one session on the PET/CT-scanner for treatment planning.

### Standardized uptake ratio (SUR)

In this trial, the SUV will be normalized by an internal image-derived standard, in order to minimize inter-study variability of FDG-uptake [18]. The cervical spinal cord will be used as the internal image-derived standard [19].

The SUR will be calculated using the following formula:

SUR_max_ = (SUV_max_in region of interest/SUV_mean_of internal standard ).

### Risk assessment of lymph nodes

#### Intervention arm

In the intervention arm, lymph nodes will be classified into three risk-levels and will be treated with a corresponding radiation dose. The FDG-PET-scan will guide risk assessment using standardized methods in order to minimize inter-institutional and inter-operator variations.
*High-risk (macroscopic tumor)*: comprises metastatic nodes that will be identified by (1) positive cytology or (2) necrosis on imaging or (3) SUR_max_ ≥ 2.0.

*Intermediate-risk*: comprises lymph nodes of borderline size having intermediate FDG-uptake and will be identified by (1) summed long- and short-axis diameter ≥ 17 mm and (2) SUR_max_ ≥ 1.5 and <2.0 and (3) cannot be high-risk (e.g. positive cytology or necrosis on imaging). These criteria are based on an in-depth risk assessment on recurrence in 1166 electively irradiated nodes in 264 patients. Not overtly pathologic lymph nodes with a summed diameter ≥ 17 mm had an increased risk to recur after elective treatment (Hazard Ratio: 17.8, 95%CI: 5.7–55, *p* < 0.001) [17].

*Low-risk (microscopic tumor)*: comprises elective lymph node regions defined in the protocol based on tumor site and stage and will be delineated according to published guidelines [20].

Retropharyngeal lymph nodes will be evaluated by traditional means as standardized FDG-PET-guided risk-assessment is not applicable to these nodes.

#### Control arm

In the control arm, no areas of intermediate risk will be identified. Lymph nodes are either assigned to the high-risk (macroscopic) volume or low-risk (elective) volume by traditional means (positive cytology or necrosis on imaging or short-axis diameter ≥ 10 mm, ≥11 mm for subdigastric nodes).

The FDG-PET-scan may be used in the decision making process by means of visual interpretation.

### Delineation and margins

For the primary tumor, the gross target volume (GTV_p_) will be delineated by traditional means using information from clinical examination and diagnostic imaging (CT and/or MRI) and will encompass all overtly macroscopic disease. In both treatment arms, a biological target volume (BTV_p_) of the primary tumor is created by means of adaptive threshold iso-contouring based on the FDG-SUR maps [19]. Gross / high-risk lymph node metastases will be delineated separately (GTV_n_).

A clinical target volume (CTV) is created to cover all routes of potential subclinical disease spread.

The GTV_p_ will be expanded by a 3D margin of 10 mm and the GTV_n_ will be expanded by a 3D margin of 5 mm (10 mm in case of extra nodal disease on imaging) in order to create the CTV_high-risk_. The CTV_high-risk_ will be adjusted for anatomical borders in which microscopic disease is unlikely to extend. No CTV expansion will be used for intermediate-risk lymph nodes as extra nodal disease is unlikely in these nodes.

To take patient set-up uncertainties into account, a planning target volume (PTV) will be created by extension of the CTV with a 3D margin of 3-5 mm (according to the participating centers protocols). Additionally, for the high-risk tumor volume an additional PTV_BGTV-high-risk_ will be created by extension of the BTV_p_ and GTV_n_ with a 3D margin of 3-5 mm. Differences in target volumes and dose prescription between the treatment arms are illustrated in Fig. 2.

### Radiation therapy regimen

Patients will be treated with accelerated external beam radiation therapy (EBRT) using volumetric modulated arc therapy (VMAT) or intensity modulated radiation therapy (IMRT) with simultaneous integrated boost (SIB) techniques to deliver multiple dose levels. The total treatment consists of 33 fractions in an overall treatment time of 33 days (5 weeks). During the first 4 weeks of treatment, 6 fractions will be delivered in 5 consecutive days per week. In the last week of treatment, 9 fractions will be delivered (i.e. 4 days bid treatment). The interval between fractions will be at least 6 h. According to the participating centers protocols, offline or online cone beam CT-scans will be made during treatment to verify correct positioning of the patient during irradiation.

Dose prescriptions for the treatment arms are shown in Table 1.

**Table 1 Tab1:** Dose prescription

Target volume	Dose (fraction dose) (Gy)		^a^EQD2 (Gy)
	Intervention-arm	Control-arm	
PTV_GBTV-high-risk_	66 (2.00)	66 (2.00)	≈ 73
PTV_CTV-high-risk_	62 (1.88)	62 (1.88)	≈ 67
PTV_intermediate-risk_	58 (1.76)	-	≈ 60
PTV_low-risk_	42 (1.27)	48 (1.45)	≈ 35 vs. 45

^a^The equivalent dose in 2 Gy fractions (EQD2) was calculated using the linear-quadratic model using an α/β = 10 Gy for tumor [34]. Differences in treatment time were taken into account by a correction of 0.6 Gy per day to compensate for tumor repopulation [35]

An accelerated fractionation schedule will be used, 33 fractions in 5 weeks (33 days)

### Follow-up

Acute toxicity will be evaluated weekly during treatment and every 2 weeks thereafter, until acute toxicity is completely healed. Acute toxicity will be scored using the common toxicity criteria v2.0 [23]. Standard oncologic follow-up visits are scheduled every 2 months during the 1st year and every 3 months during the 2nd year, after which study participation ends. However, oncologic follow-up will continue every 4 months during the 3rd year and twice annually until at least 5 years of follow-up. During oncologic follow-up visits, late toxicity, recurrence and survival will be evaluated. Late toxicity will be scored using the RTOG/EORTC late radiation morbidity scoring criteria [24].

Periodical study visits will be scheduled once before treatment and at 3, 6, 12 and 24 months after radiation therapy. Subjects will undergo assessment of the swallowing function, thyroid- and salivary glands function and quality of life questionnaires will be completed.

A schedule of study procedures is shown in Table 2.

**Table 2 Tab2:** Schedule of study procedures

Procedure	Before treatment	During treatment	Months after treatment				
			0	3	6	12	24
Planning FDG-PET/CT-scan	x						
Acute toxicity (CTC v2.0)		x	x	x			
Late toxicity (RTOG-EORTC)				x	x	x	x
Assessment of thyroid function (Blood analysis)	x				x	x	x
Dysphagia related quality of life (PSS-HN, SWAL-QOL)	x			x	x	x	x
Assessment of swallowing function (Water swallowing test)	x			x		x	x
Xerostomia related quality of life (GRIX)	x			x	x	x	x
Assessment salivary gland function (sialometry, sialochemistry)	x			x		x	x
General quality of life (EORTC QLQ-C30, EORTC H&N35)	x			x	x	x	x
Assessment of recurrence			each follow-up visit				

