Because bilateral irradiation of cervical lymph node regions contributes to dysphagia, xerostomia and thyroid dysfunction in a dose dependent way [8, 9], dose reduction to these regions can open a window of opportunity to reduce toxicity and improve quality of life after treatment [10].

A treatment planning study performed at the Radboudumc showed that de-escalation of the elective dose as proposed in this study protocol, can reduce the dose to normal tissues such as the swallowing musculature, thyroid- and salivary glands (unpublished data). Normal tissue complication probability models from the available literature [11–15] showed that a relevant decrease in toxicity can be expected for xerostomia (absolute up to 14%, relative risk up to 39%), dysphagia (absolute up to 12%, relative risk up to 67%) and hypothyroidism (absolute up to 20%, relative risk up to 50%).

Given these considerations we believe that the traditional binary dose prescription in head and neck cancer is outdated. In this trial, a more gradual dose prescription will be used with de-escalation of the elective radiation dose and the introduction of an intermediate dose-level in the treatment of head and neck cancer. The aim is to investigate whether such a treatment will result in less radiation sequelae and improved quality of life after treatment (expressed as a normalcy of diet) without compromising the recurrence rate in electively irradiated lymph nodes.

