### Endpoints

Primary endpoint (toxicity): ‘normalcy of diet’ at 1 year after treatment, measured using the performance status scale for patients with head and neck cancer (PSS-HN) [16].

Secondary endpoint (safety): actuarial rate of recurrence in electively irradiated lymph nodes at 2 years after treatment.

Other endpoints:

Acute toxicity (mucositis, dysphagia and skin reaction).

Late toxicity (with focus on xerostomia, dysphagia and hypothyroidism).

Quality of life (general-, xerostomia- and dysphagia related quality of life).

Recurrence (local, regional, loco-regional and distant).

Survival (overall, disease specific and disease free).

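### No CTC or RTOG/EORTC grade is scheduled before treatment, so new or worsened toxicity cannot be derived on those scales (other endpoints only)

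*Protocol article*

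**What the plan says.** The Follow-up section of the protocol article fixes scale and timing for both kinds of graded toxicity.

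- **Acute:** "Acute toxicity will be scored using the common toxicity criteria v2.0", and "Acute toxicity will be evaluated weekly during treatment and every 2 weeks thereafter, until acute toxicity is completely healed". Table 2 marks this row during treatment and at months 0 and 3.
- **Late:** "Late toxicity will be scored using the RTOG/EORTC late radiation morbidity scoring criteria", and "During oncologic follow-up visits, late toxicity, recurrence and survival will be evaluated". Table 2 marks this row at 3, 6, 12 and 24 months.

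Neither row has a mark under Before treatment, and the text agrees with the table. A pre-treatment visit does exist: "Periodical study visits will be scheduled once before treatment and at 3, 6, 12 and 24 months after radiation therapy". At these visits "Subjects will undergo assessment of the swallowing function, thyroid- and salivary glands function and quality of life questionnaires will be completed". Table 2 gives a pre-treatment mark to thyroid bloods, PSS-HN and SWAL-QOL, the water swallowing test, GRIX, sialometry and sialochemistry, and the EORTC questionnaires.

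The Endpoints section places graded acute toxicity (mucositis, dysphagia, skin reaction) and graded late toxicity (focused on xerostomia, dysphagia and hypothyroidism) among the other endpoints. The primary endpoint is PSS-HN normalcy of diet at 1 year. The safety endpoint is recurrence in electively irradiated nodes at 2 years.

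**The concern.** Eligible patients have T2-4 tumours of the larynx, oropharynx or hypopharynx, so some can be expected to have swallowing problems before the first fraction. A lower elective dose cannot prevent a symptom that predates treatment. If such a symptom persists at the grade being counted, it appears in both arms and shrinks the visible difference.

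The usual remedy is to analyse new or worsened grade, or to adjust for the starting grade. Both need a starting grade on the same scale, and the schedule does not collect one. A later analysis plan can choose how to handle the grades, but it cannot supply a score that was never taken. The matter therefore has to be settled in the visit schedule, before each patient starts treatment.

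At stake is the sensitivity of the acute dysphagia and late dysphagia and xerostomia comparisons. These support the trial's aim of fewer radiation sequelae.

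**Working it through.** **The plan's own figure.** The article states no sample size or power for the graded endpoints, so there is nothing to reproduce. The 300 patients are sized for the primary endpoint, which is not a CTC or RTOG/EORTC grade and has a pre-treatment measurement.

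**Inputs.**
- Arms of 100 (control) and 200 (intervention): 300 patients randomised 2:1 (Sample size calculation).
- Predicted reduction in dysphagia: up to 12 points absolute and up to 67% relative (Background). Taken as one model, the control risk is 12/0.67 = 17.9% and the intervention risk 17.9 − 12 = 5.9%, rounded to 18% vs 6%. The pairing is an assumption, because both figures are maxima drawn from several models.
- b, the share of patients with prior dysphagia that persists at the counted grade. The documents give no value, so a range of 0 to 30% is shown.
- Two-sided significance level of 0.05, assumed for this endpoint.

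**Dilution.** If b is the same in both arms, the observed risk is b + (1 − b)p, and the observed difference is (1 − b) times the true one. At b = 20%:
- control: 0.20 + 0.80 × 0.18 = 0.344
- intervention: 0.20 + 0.80 × 0.06 = 0.248
- difference: 0.096 instead of 0.12; risk ratio: 0.248/0.344 = 0.72 instead of 0.33

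**Power at b = 20%, normal approximation.**
- pooled risk: (34.4 + 49.6)/300 = 0.280
- standard error under no difference: √(0.280 × 0.720 × (1/100 + 1/200)) = 0.0550
- standard error under the alternative: √(0.344 × 0.656/100 + 0.248 × 0.752/200) = 0.0565
- power: Φ((0.096 − 1.96 × 0.0550)/0.0565) = Φ(−0.21) = 0.42

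**Across the range.** Power is from 200,000 simulations of the pooled z-test. The last column tests only patients free of dysphagia at baseline.

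| b | Observed rates | Difference (points) | Power, everyone counted | Power, baseline-free patients |
|---|---|---|---|---|
| 0 | 18.0% vs 6.0% | 12.0 | 0.89 | 0.89 |
| 5% | 22.1% vs 10.7% | 11.4 | 0.74 | 0.87 |
| 10% | 26.2% vs 15.4% | 10.8 | 0.61 | 0.86 |
| 20% | 34.4% vs 24.8% | 9.6 | 0.42 | 0.81 |
| 30% | 42.6% vs 34.2% | 8.4 | 0.30 | 0.77 |

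The normal approximation gives 0.87 at b = 0 and agrees with the simulation to within about one point in the other rows of the everyone-counted column. A formula with unpooled variance gives lower values at b = 20%: 0.40 with everyone counted and 0.73 in baseline-free patients.

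**Which endpoints are touched.** Xerostomia is not among the listed acute toxicities, so for dry mouth only the late RTOG/EORTC grade is concerned. Hypothyroidism has a pre-treatment blood test.

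**The case against.** A reader might infer that pre-existing dysphagia or dry mouth will be counted as radiation toxicity. The article does not say so. It gives no rule for attribution, worst grade or cut-off for the grades, and such rules commonly sit in the full protocol or the analysis plan, which are not shown. It is also understandable that a scale for late radiation morbidity has no score before radiation. What stands is narrower: on these two scales, change from the start cannot be derived.

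A reader might also infer that prior symptoms can never be separated from treatment effects. That goes too far. PSS-HN, SWAL-QOL, the water swallowing test and GRIX are all taken before treatment and allow adjustment. They are different instruments and cannot yield a change in clinician grade, and salivary flow is measured in only some centres. Even so, knowledge of prior symptoms is not missing.

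The size is also open to challenge.
- Only dysphagia that persists counts. If 20% have it at the start and half persist, b is 10% and power about 0.61. If a quarter persist, b is 5% and power about 0.74.
- The 18% vs 6% is a best case, not an expected trial result.
- The baseline-free column describes a subset analysis. No gain has been computed for the covariate-adjusted analysis.
- The documents give no basis for expecting dry mouth caused by the tumour.

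Finally, randomisation balances prior symptoms in expectation, and the article claims power only for the primary and safety endpoints. All of these objections stand. They limit the reach of the point but do not remove the gap in the schedule.

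**Conclusion.** The point holds in limited form. The text and Table 2 both omit a pre-treatment CTC or RTOG/EORTC grade, so new or worsened toxicity cannot be derived on those scales for the graded endpoints. Persistent tumour-related dysphagia would raise the absolute rates in both arms and reduce the sensitivity of the graded comparison. No bias towards either arm is expected.

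The size is unknown. In the illustration, even b = 5% costs about 15 points of power (0.89 to 0.74), and b = 20% costs nearly half (0.89 to 0.42). This rests on an assumed b that is equal in both arms, on persistence at the counted grade, on a binary grade analysed without regard to baseline, and on the paired maxima from the Background. This is a cheap improvement of low priority.

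**What to change.** 1. In Table 2, add a Before treatment mark for the CTC dysphagia and mucosal items and for the dysphagia and xerostomia items relevant to the RTOG/EORTC scale, scored at the pre-treatment study visit that already exists.
2. State that graded toxicity is analysed as new or worsened grade relative to that score, or with the baseline grade as covariate.
3. For patients already enrolled without a baseline grade, adjust graded dysphagia for pre-treatment PSS-HN/SWAL-QOL and late xerostomia for pre-treatment GRIX. These data are already collected.

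The cost is a few minutes of scoring per patient, one table edit and one sentence on the analysis. Patients already at the counted grade add little to a new-toxicity analysis, so the covariate-adjusted version should be kept alongside it. The sample size does not change.
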